### Consent

Patients who agree to participate in the project will be consented by a member of the treating team, local PI or local sub-PI affiliated with this project. The participant’s competence and capacity to consent to the study will be assessed by one of these members. Any patient who is not able to give valid, informed consent for themselves will not be considered for inclusion. Patients will be asked to consent to the collection of biospecimens and associated data as detailed in section 5a. They will also be asked to consent to the storage and future use of these samples and data. All procedures will be conducted in accordance with the Declaration of Helsinki. Please refer to the Patient Information and Consent form for more details.

The consent process will occur significantly ahead of any clinical procedure. The clinician/investigator will allow time to answer any questions from the patient regarding the project and provide the patient time to consider their involvement. The clinician will also emphasize that the standard of care will not be altered in any way, regardless of the patient’s consent. On the morning of staging laparoscopy/endoscopy and definitive surgery, the project will be discussed again with participants. They will be given the opportunity to ask questions. For participants who have already given consent, local investigators will verbally re-affirm their consent prior to the start of their procedure and the collection of samples. For potential participants who have not yet signed the consent form, they will be asked if they wish to sign the form before their procedure. Patients are under no obligations to sign the consent form, and for those who have signed and then changed their mind, they may withdraw consent at any time (See below 7b, Handling of withdrawals for further detail).

The clinician/investigator will facilitate signing of the PICF and provide the participant with a copy. A copy of the PICF will be added to the participants medical records. The original PICF will be digitised and stored locally in keeping with each institution’s practices. The hardcopy will be kept in a locked filing cabinet in a locked office.

For any prospective participant recruited under OMEGCA, individual explicit consent will be sought as outline above. For participants from Project No 18/211, ‘*Improving outcomes in gastroesophageal cancer*’, consent has already been provided for the collection and use of their biospecimens and clinical data under HREC/44873/PMCC-2018. In particular, this includes DNA analysis for biomarker studies. Moreover, this consent included the use of their biospecimens and clinical data in other/future projects without the need for repeated consenting. Furthermore, it is impractical to obtain repeated consents from this cohort as, due to the nature of the disease being studied, a considerable number of these patients may be deceased. Additionally, the required clinical data have already been collected as part of routine care and will be de-identified, carrying negligible risk to participant confidentiality. It is therefore reasonable to assume that there is no likely reason for thinking that participants would not have consented if circumstances had allowed for them to be asked.

# **Participant Safety and Withdrawal**

### Risk Management and Safety

POTENTIAL RISKS – BLOOD COLLECTION:

Having a blood sample taken may cause some discomfort, bruising, minor infection or bleeding. All blood samples will be taken by trained personnel who are qualified to manage any such problems. However, in most cases, taking blood for this study will not involve any additional discomfort or risk since wherever possible this will be collected through the cannula which is routinely inserted as part of the standard endoscopy/surgery procedure.

POTENTIAL RISKS – COLLECTION OF PERITONEAL FLUID:

There is no additional risk or burden to the patient from collecting the waste fluid from their peritoneal wash that is performed as part of their standard of care.

POTENTIAL RISKS – TISSUE BIOPSIES:

Taking extra biopsies has minimal risk of harm as the participants are already having an endoscopy and the biopsies themselves are very small. However, taking biopsies for research means the endoscopy/laparoscopy will take a few minutes longer.

POTENTIAL RISKS – GENETIC INFORMATION:

There is a very small possibility that the research may result in new genetic information about a participant’s specific disease or their risk of getting other conditions. If research findings are made that may have significant implications for a participant or their family, we will submit a full report to the Peter MacCallum Human Research Ethics Committee and the appropriate established procedures will be followed. Participants will be given the choice as to whether or not they wish to know of any important results that has significant implications for them or their family. We will also ask participants if they want the information to be given to a member of their family if they cannot be contacted directly. We will not give any information about the participant to members of their family without their permission. It is possible that in the future genetic information from this study may affect a participant or their family when taking out a new life or income protection insurance policy or increase an existing life or income protection insurance policy. We will not pass on genetic information about a participant to anyone, including family members, without their written permission unless required to by law.

OVERALL RISK MITIGATION STRATEGIES:

To ensure smooth and safe collection of patients’ specimens, all specimen samples (blood, tissue biopsies and peritoneal lavage) will be collected by qualified clinicians who are well informed of the collection protocol. Blood collection at staging laparoscopy and surgical resection will be done by anaesthetists involved in the patient’s care. Tissue biopsies and peritoneal lavage will be collected by a member of the surgical team. Overall, in the unlikely event that something does arise that may significantly impact a patient’s welfare, we will follow established procedures and submit a full report to the Human Research Ethics Committee to seek advice on the most appropriate course of action.

### Handling of Withdrawals

Patients may choose to withdraw from the study at any time at their own volition. The following scenarios may apply:

- Withdrawal from study completely
- Withdrawal from further biospecimen collection with already collected biospecimen and clinical data
- Withdrawal from further clinical data collection with already collected biospecimen and clinical data

*Withdrawal from study completely*: Should a patient withdraw consent from further participation in this study, they will undergo routine clinical care without any additional biospecimen collection and all clinical data collection relating to the patient will cease. Wherever possible, all collected and analysed data will be electronically and/or manually deleted from our study records. All collected tissues and fluid will be disposed of appropriately. This will not impact on our ability to use samples and data obtained from other participants and therefore will not have any overall adverse impact on our project. Occasionally, it may not be possible to destroy material that has already been processed.

*Withdrawal from further biospecimen collection with already collected biospecimen and clinical data*: Should a patient choose to remain in the study, they will undergo routine clinical care without any additional specimen collection. However, the collection of their clinical data will continue, and the already collected specimen will be included in the final analysis.

*Withdrawal from further clinical data collection with already collected biospecimen and clinical data*: Should a patient choose to remain in the study, they will undergo routine clinical care without any additional clinical data collection. However, where appropriate, the already collected specimen and clinical data will be included in appropriate analysis e.g. initial validation experiments.

### Replacements

Due to the relatively low sample size required to address our primary endpoint, we plan to replace all withdrawn participants through additional recruitment to ensure that this study meets the sample size calculated in 8a.

# **Statistical Methods**

### Sample Size Estimation & Justification & Power Calculation

POWER JUSTIFICATION:

OMEGCA will have 4 observational cohorts as listed below:

- Group 1: Peritoneal lavage cytology-negative & ptDNA-negative
- Group 2: Peritoneal lavage cytology-negative & ptDNA-positive
- Group 3: Peritoneal lavage cytology-positive & ptDNA-negative
- Group 4: Peritoneal lavage cytology-positive & ptDNA-positive

However, as the primary objective of this study is to evaluate the clinical utility of ptDNA as a biomarker to predict the primary endpoint (2-year DFS) in gastroesophageal cancer patients with no apparent micro-metastatic disease in the peritoneum (using current ‘best practice’ staging methods), we have powered this study to compare groups 1 and 2, as these are the patients with *peritoneal lavage cytology-negative* disease. Accordingly, we deemed a 30% absolute DFS difference at 2 years post staging laparoscopy as clinically significant between groups 1 and 2. This is based on our hypothesis that patients who are ptDNA-positive should by definition have cytology-positive disease, even if this was not detected. The conservative estimate of 2-year DFS in patients who are cytology-positive versus cytology-negative is 40% versus 70%, respectively. Using our pilot data (Figure 3), we anticipate approximately 1 in 8 patients who is cytology-negative will be ptDNA-positive, this means an enrolment ratio of 7 to 1 in groups 1 and 2, respectively. To detect a 30% absolute difference in 2-year DFS between these two groups, we would need to enrol 200 patients with 175 patients in group 1 (ptDNA-negative arm) and 25 patients in group 2 (ptDNA-positive arm) to reach 80% statistical power at an alpha <0.05.

INTERIM ANALYSIS:

Based on centre volume, the number of participating sites, the number of patients already recruited on 18/211, and accounting for a 30% participant attrition rate, we anticipate to complete patient recruitment in 2 years. We will perform an interim analysis at 1 and 2 years after commencement of recruitment to ensure that the enrolment ratio between groups 1 (cytology-negative/ptDNA-negative) and 2 (cytology-negative/ptDNA-positive) is on-track (*Figure 4*). This will be measured by analysing the proportion of patients who are cytology-negative and ptDNA-positive. If the ratio of ptDNA-positive/cytology-negative is ≥10%, then recruitment of patients will continue to the target of 200. If this ratio is <10%, we will adjust our recruitment strategy accordingly. Additionally, we will perform an interim analysis at 3 years after commencement of patient recruitment (i.e. ≥1-year DFS data) to compare DFS between groups.

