### Study Objectives

PRIMARY OBJECTIVE:

1. To determine whether pre-treatment ptDNA, detected using genomic and methylomic approaches, predicts DFS in gastroesophageal cancer patients.

SECONDARY OBJECTIVES:

1. To analyse the ability of methylomic and genomic assays, in comparison and in combination, to detect ptDNA and predict DFS and OS.
2. To compare the performance of ptDNA vs. conventional staging methods (PLC, PET/CT) to predict histopathological features of the tumour, patterns of disease recurrence, DFS and OS.

EXPLORATORY OBJECTIVES:

1. To compare the cost-effectiveness of genomic vs. methylomic approaches to detect ptDNA to inform translation into clinical practice.
2. To compare ptDNA detection rates before (at time of PLC) and after (at time of surgical resection) neoadjuvant therapy.
3. To curate and catalogue actionable molecular targets identified from whole exome sequencing of peritoneal wash fluid to inform future clinical trials.
4. To compare ptDNA versus circulating tumour DNA (i.e. plasma) to predict sites and patterns of disease recurrence.

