### Study Endpoints

PRIMARY ENDPOINTS:

- 2-year disease free survival (DFS) (*Objective 1*)

SECONDARY ENDPOINTS:

- *Survival*: 3-year peritoneal DFS, 3-year overall survival (OS), 5-year DFS, and 5-year OS (*Objectives 2 & 3*)
- *Peritoneal lavage cytology status*: present/absent/indeterminant (*Objective 3*)
- *Imaging (CT/PET scans) and endoscopy*: Location of disease recurrence (*Objective 3*)
- *Primary tumour histopathological features*: T-stage, N-stage, grade, lymphovascular invasion, perineural infiltration, histological subtypes, tumour size, and tumour regression grading (*Objective 3*)
- *Cost effectiveness*: accounting for assay performance, direct-costs, technical aspects, clinical impact, and quality-adjusted life years (*Objective 4*)
- *Genomic analysis of ptDNA*: mutant allelic frequency thresholds, presence of actionable therapeutic targets against a registry of clinically proven and experimental therapies (*Objectives 5 & 6*)
- *ctDNA status*: present/absent, mutant allelic frequency threshold (*Objectives 7*)

DEFINITIONS FOR PRIMARY AND SECONDARY ENDPOINTS:

- *Disease recurrence*: recurrence of disease after surgical resection of the primary tumour, in any site, detectable on clinical, endoscopic, and/or imaging investigations.
- *Disease free survival*: Time from date of surgical resection to date of disease recurrence
- *Overall survival*: Time from date of surgical resection to date of death
- *Cancer staging*: T, N and M stage for CT/PET scans and histopathology will be according to AJCC 8^th^ Edition for Gastric and Gastroesophageal Junction Cancers

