# **Study Design**

### Study Type, Design, Schedule & Methodology

STUDY TYPE:

- Prospective non-interventional cohort study
- This study will include a cohort of patients who have undergone identical biospecimen collection, clinical treatments, and follow-up from Project No: 18/211, entitled ‘*Improving outcomes in gastroesophageal cancer*’ (HREC/44873/PMCC-2018)

ABOUT PROJECT NO: 18/211:

- Relevant to this study, project No: 18/211, entitled ‘*Improving outcomes in gastroesophageal cancer*’ (HREC/44873/PMCC-2018) was in part (as it was multi-facetted with different aims), a multi-centre biospecimen (tumour and normal tissue, blood, and peritoneal fluid) and clinical data collection project.
- Project 18/211 established the collaborative research network and generated the critical pilot data (11 patients) for this proposed study. The patient cohort recruited through Project 18/211 are identical to this proposed study.
- To avoid wastage of patient samples, research cost, human resources, and time, we propose that eligible patients who have undergone identical biospecimen collection, clinical treatments, cancer surveillance and follow-up in Project 18/211 as this proposed study, to be combined for the purpose of data analysis.

STUDY PERIOD:

- Participant recruitment: 2 years
- Clinical follow-up: Follow-up for 5 years after the last enrolled patient

STUDY SAMPLE SIZE:

- Merging of participants from this study and Project No: 18/211
- Combine total participant ≥200 based on power calculation, please see below and in section 8.

STUDY POPULATION:

- All patients with gastroesophageal junction and gastric cancer
- ≥ 18 years-of-age
- Without distant organ, non-regional nodal or gross peritoneal metastases
- Undergoing staging laparoscopy with peritoneal lavage cytology (PLC)
- Undergoing curative-intent treatment (either upfront surgery or chemo/radiotherapy and surgery) for their cancer

DESIGN SUMMARY TO ACHIEVE OBJECTIVES:

- This prospective, multicentre observational cohort study will enrol patients undergoing PLC and subsequent curative-intent treatment for gastroesophageal cancer.
- Tumour and normal (stomach and oesophagus) tissue biopsies, blood, and peritoneal lavage fluid will be collected during pre-treatment staging for all patients.
- A subset of patients (those who undergo neoadjuvant chemo/radiotherapy) will have tumour tissue, blood and peritoneal lavage fluid collected at surgery.

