### Inclusion Criteria

- All patients ≥18 years-of-age at time of signing consent
- Have a histologically confirmed diagnosis of one of the following:
  - Gastric adenocarcinoma
  - Gastroesophageal junction adenocarcinoma
- Is undergoing staging laparoscopy and peritoneal lavage cytology
- Provides informed consent

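### The primary endpoint has two time origins, staging laparoscopy for power and surgical resection by definition, and under the resection origin patients never resected have no DFS or OS time

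*Protocol*

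**What the plan says.** **Effect size (section 8a, power justification).** "we deemed a 30% absolute DFS difference at 2 years post staging laparoscopy as clinically significant between groups 1 and 2". The assumed 2-year rates are 70% (group 1, cytology-negative and ptDNA-negative) and 40% (group 2, cytology-negative and ptDNA-positive), with 175 and 25 patients.

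**Endpoint definitions (section 4c).** DFS is "Time from date of surgical resection to date of disease recurrence". OS is "Time from date of surgical resection to date of death". Recurrence means "recurrence of disease after surgical resection of the primary tumour, in any site".

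**Objective (section 4b).** "To determine whether pre-treatment ptDNA, detected using genomic and methylomic approaches, predicts DFS in gastroesophageal cancer patients".

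**Entry and sampling.** The entry criterion in section 6b is "Is undergoing staging laparoscopy and peritoneal lavage cytology"; a completed resection is not required. Section 5a says that "blood, and peritoneal lavage fluid will be collected during pre-treatment staging for all patients". Treatment can come between sampling and surgery: "A subset of patients (those who undergo neoadjuvant chemo/radiotherapy) will have tumour tissue, blood and peritoneal lavage fluid collected at surgery".

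**The concern.** Both statements of the time origin are current text about the primary endpoint, and they differ. This is more than a detail left open for an analysis plan, because the protocol fixes the origin twice.

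The choice matters because the biomarker is read at staging and some patients then have neoadjuvant therapy. A patient who progresses, dies or is found unresectable in that interval has a ptDNA result but, under section 4c, no start date for DFS or OS. An analysis that follows section 4c compares ptDNA groups only among those who reached resection. If ptDNA marks occult peritoneal disease, as the protocol hypothesises, reaching resection may itself depend on ptDNA status. The group most exposed is group 2, which has only 25 patients.

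**Working it through.** **1. The protocol's own figure.** Inputs from section 8a: 70% vs 40%, 175 vs 25, alpha 0.05 (taken as two-sided), power 80%.
- Two-sided Fisher exact test, exact binomial power: 175 vs 25 gives 80.9%; 168 vs 24 gives 78.5%. The stated 200 reproduces, so the sample-size arithmetic is not at fault.
- Pooled normal approximation: power = Φ[(|p1 − p2| − 1.96·s0)/s1], with s0 = √(p̄(1 − p̄)(1/n1 + 1/n2)) and s1 = √(p1(1 − p1)/n1 + p2(1 − p2)/n2). Here p̄ = (122.5 + 10)/200 = 0.6625, s0 = 0.1011 and s1 = 0.1039. Then (0.30 − 0.198)/0.1039 = 0.98, giving 83.6%. This is the baseline for the scenarios below.

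**2. The passages side by side.**

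| Item | Section | Anchor |
|---|---|---|
| Enrolment | 6b | staging laparoscopy |
| ptDNA sampling for the primary objective | 5a | staging, before treatment |
| 30-point difference | 8a | 2 years from laparoscopy |
| DFS and OS | 4c | resection |

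The interim analysis text in section 8a also fits a clock that starts near enrolment. Recruitment lasts 2 years, and 3 years after it opens every patient is expected to have at least 1 year of DFS data: 3 − 2 = 1. For the last patients enrolled, that fails if the clock starts only after neoadjuvant therapy and surgery.

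**3. Effect on power if only resected patients count.** The protocol gives no non-resection rates. Those below (r1 in group 1, r2 in group 2) are assumptions. Remaining numbers are 175(1 − r1) and 25(1 − r2).
- Scenario A: 70%/40% still hold among the resected.
- Scenario B: 70%/40% apply from laparoscopy and every unresected patient is a failure. The resected-only rates are then 0.70/(1 − r1) and 0.40/(1 − r2).

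| r1 / r2 | n1 / n2 | Power, A | Resected-only rates, B | Gap, B | Power, B |
|---|---|---|---|---|---|
| 10% / 10% | 157.5 / 22.5 | 79.7% | 77.8% vs 44.4% | 33 points | 90% |
| 10% / 20% | 157.5 / 20 | 75.7% | 77.8% vs 50.0% | 28 points | 74% |
| 10% / 30% | 157.5 / 17.5 | 71.0% | 77.8% vs 57.1% | 21 points | 48% |
| 10% / 40% | 157.5 / 15 | 65.3% | 77.8% vs 66.7% | 11 points | 19% |

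**4. How far the model matters.** Scenario B gives status 24 months after laparoscopy, not 24 months after resection. Two variants assume 4 months from laparoscopy to surgery.
- Losses of 5% and 20%: resected-only rates are 0.70/0.95 = 73.7% and 0.40/0.80 = 50.0% in 166 vs 20, with power 59%. Carried to 24 months after resection at a constant hazard, they are 0.737^(24/20) = 69% and 0.50^(24/20) = 44%, a gap of 26 points with power about 63%.
- One constant hazard per group from laparoscopy: 175 × 0.70^(4/24) ≈ 165 and 25 × 0.40^(4/24) ≈ 21 reach surgery. Two-year DFS from resection stays 70% vs 40%, and power is about 78%.

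**The case against.** **Nothing in the protocol says that unresected patients are excluded.** This is correct. A reader might infer a formal exclusion rule, but there is none. The gap follows from applying section 4c as written; with the section 8a origin these patients would have a start date. What stands is that the two sections conflict and no rule covers these patients.

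**The population is surgical and the rationale is recurrence after surgery.** Section 5a describes curative-intent treatment that includes surgery, palliative intent is excluded, and the background cites early recurrence after resection. DFS from resection is therefore a legitimate, narrower question, and it goes too far to say that the study would no longer inform staging. But surgery planned at entry is not surgery completed, and restricting to the resected selects on something that happens after the biomarker is measured.

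**Attrition and replacement may absorb the loss.** Section 8a allows 30% attrition when projecting recruitment time, and section 7c replaces withdrawn participants. Neither mentions unresected patients. Replacing them could restore numbers but would not undo the selection.

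**The contrast need not shrink.** This also stands. Equal 10% loss widens the gap to 33 points in scenario B, and the constant-hazard variant leaves it at 30. Shrinkage requires heavier loss in group 2. The protocol's hypothesis makes that plausible, but no figure in it establishes it.

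**Surgery is the usual origin for DFS.** If so, the section 8a landmark is wrong and the comparison must be declared conditional on resection. The text has to change either way.

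**Conclusion.** The point holds as a contradiction in the primary endpoint. The effect size is set from laparoscopy, DFS and OS are defined from resection, and under the section 4c definition patients who fail before surgery have no outcome time. That much rests on the text alone.

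The size is conditional. Against a baseline of 80.9% (Fisher) or 83.6% (pooled normal), assumed losses of 10% in group 1 and 20–40% in group 2 give power of about 65–76% if 70%/40% hold among the resected. Power is about 19–74% if those rates run from laparoscopy and every unresected patient is a failure. Equal loss leaves the contrast intact. A reader might take a single figure such as 59%, or a necessarily smaller difference, as established. The protocol supports neither, because it gives no non-resection rates and the answer changes with the failure model.

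It should be settled before the DFS comparison planned for 3 years after recruitment opens.

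**What to change.** - Use one time origin in sections 4c and 8a. Start the primary time-to-event endpoint and OS at staging laparoscopy for every enrolled patient in groups 1 and 2.
- For the primary endpoint, count as events pre-resection progression, a finding of unresectable or metastatic disease, recurrence, and death. This is in effect event-free survival and should be named so. Including death is a further change, since section 4c currently names only recurrence.
- Keep DFS from resection as a secondary analysis, labelled conditional on resection.
- State in section 8a that 70%/40% are assumed to apply from laparoscopy. All 175 + 25 patients then stay in the comparison and the 80.9% stands on that assumption.

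**Cost.** The laparoscopy date and the pre-resection outcome must be recorded for every patient, including the roughly 100 from Project 18/211. The section 5a schedule marks survival and recurrence data only at long-term follow-up, and surveillance is timed from surgery, so a data field for pre-resection outcome is likely to be needed. No study visits need be added. The primary result becomes less directly comparable with series that start at surgery, which the secondary analysis addresses.
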